## Abstract

**Background:**

There is increasing community and government recognition of the magnitude and impact of adolescent depression. Family based interventions have significant potential to address known risk factors for adolescent depression and could be an effective way of engaging adolescents in treatment. The evidence for family based treatments of adolescent depression is not well developed. The objective of this clinical trial is to determine whether a family based intervention can reduce rates of unipolar depressive disorders in adolescents, improve family functioning and engage adolescents who are reluctant to access mental health services.

**Methods/Design:**

The Family Options study will determine whether a manualized family based intervention designed to target both individual and family based factors in adolescent depression (BEST MOOD) will be more effective in reducing unipolar depressive disorders than an active (standard practice) control condition consisting of a parenting group using supportive techniques (PAST). The study is a multicenter effectiveness randomized controlled trial. Both interventions are delivered in group format over eight weekly sessions, of two hours per session. We will recruit 160 adolescents (12 to 18 years old) and their families, randomized equally to each treatment condition. Participants will be assessed at baseline, eight weeks and 20 weeks. Assessment of eligibility and primary outcome will be conducted using the KID-SCID structured clinical interview via adolescent and parent self-report. Assessments of family mental health, functioning and therapeutic processes will also be conducted. Data will be analyzed using Multilevel Mixed Modeling accounting for time x treatment effects and random effects for group and family characteristics. This trial is currently recruiting. Challenges in design and implementation to-date are discussed. These include diagnosis and differential diagnosis of mental disorders in the context of adolescent development, non-compliance of adolescents with requirements of assessment, questionnaire completion and treatment attendance, breaking randomization, and measuring the complexity of change in the context of a family-based intervention.

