**Figure 1 F1:**
[figure not shown]
CONSORT flow diagram of progress through the phases of the Family Options trial.

Enrollment into the trial will involve an intake worker conducting an initial telephone assessment with a parent or caregiver of the young person. This assessment will include: family demographic information, a genogram, a screen for inclusion and exclusion criteria, a the KID-SCID Mood Episodes Module B as reported by parents, and information on the young person and parent/s current mental health status and support services psychotropic medications, recent alcohol and other drug use and violence within the family, and risk assessments including suicide and self-harm risk. If the family is deemed eligible for participation in the trial, the intake worker will then confirm eligibility by administering selected modules of the KID-SCID to the young person. The selected modules are those for Major Depressive Disorder, Minor Depressive Disorder, and Dysthymic Disorder [28]. If the young person meets the inclusion criteria, the intake worker will then allocate to treatment condition using the randomized allocation sequence. Participants will be advised verbally and in writing that they will be free to withdraw at any stage upon request. Attempts will be made to assist families to find an alternative source of treatment, where possible, should they choose to withdraw at any stage.

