### Assessments and outcome measures

The following measures will be administered to assess the previously described study hypotheses across three time points during the trial: enrollment in the trial (T1), completion of treatment (T2), and three months post-treatment completion (T3). To maximize the clinical validity of the outcome evaluations, these assessments will involve both clinician administered and self-report measures. These measures have been chosen based on piloting in previous trials and in terms of minimizing participant burden while maximizing sensitivity to clinical change across key domains.

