### Sample size and power

The trial aims to recruit a total of *n* = 160 participants. Based on pilot work and previously conducted clinical trials of family-based interventions compared to treatment-as-usual conditions, it has been estimated that it is possible to generate an effect size of *d* = 0.63 in reduction of mental health symptoms, which is equivalent to 14% increase in the odds of remission [45]. Out pilot data also indicates that treatment type by time interaction is able to produce up to 50% remission in depression diagnosis, over and above treatment type. With an alpha of 0.05 and power level of 0.90 for two-tailed tests, intraclass correlation coefficient (ICC) of 0.17 for within therapy group variation (estimated from our pilot data), and estimated 10% of variation in the main outcome accounted for by other variables in the model (treatment arm, time, parental socioeconomic status), the minimum sample size required equates to *n* = 57 per treatment arm. Based on pilot studies, an attrition rate of 20 to 25% is anticipated. Therefore, a minimum of 80 participants into each of the two treatment conditions will be recruited. Comparisons will be undertaken between those who drop out and those who are retained in order to assess for attrition bias.

With respect to our secondary hypotheses, anticipated final sample size of 114 individuals, will also allow us to detect small effect size (d = 0.23) for the treatment arm by time interaction for continuous outcomes, with 90% power and alpha level of 0.05, assuming ICC of 0.20 for within-person (between-assessment) and ICC of 0.07 for within therapy group variation (estimated from our pilot data).

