### Statistical analysis plan

Repeated measures binomial data will be analyzed over three time points using a binary logistic regression within the Generalized Linear Mixed Model (GLMM). The model will be fitted in STATA (xtmelogit). For any continuous-scale data we will use a linear mixed model approach in STATA. For both types of data we will explore variance-covariance structures for the evaluations within an individual. Clinical significance and an index of reliable change will be calculated for each measure using the criteria of Jacobson and Truax [46]. Findings will be analyzed in terms of standardized mean differences and effect sizes achieved will be compared to existing high quality trials to determine relative efficacy of this intervention. Multivariable multilevel models will also explore other covariates on the relationship between treatment arm and study outcomes, with a view to improving the intervention and specifying its ideal target population. Data will be stored in a locked cabinet, and a password protected computer file will contain de-identified (coded) data. A proportion of the data will be double-entered, and range checks will be performed for accuracy checking. Intention-to-treat analysis will be used with the last observation carried forward as a conservative estimate of outcome when data are missing at follow-up.

In addition, analysis of qualitative data from the transcribed interviews of participants who did not take up the option of treatment following intake/assessment, discontinued treatment, or completed treatment will be undertaken. Thematic analysis of participants’ accounts of their experience of the intake/assessment process and reasons for either engaging with or distancing themselves from the treatment offered will be undertaken. Meanings participants assign to the process will also be extracted from the data. Analysis of the data relevant to the phenomena of interest will assist in the identification of barriers to engagement and change for families.

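### For the continuous secondary outcomes, a therapy-group random intercept common to all visits would not protect the arm-by-time test, because the groups form only after T1

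*Protocol article*

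**What the plan says.** The abstract of the protocol article announces "Multilevel Mixed Modeling accounting for time x treatment effects and random effects for group and family characteristics". The section on statistical analysis gives a logistic mixed model for binary data and a linear mixed model for continuous data. For both, the authors say "we will explore variance-covariance structures for the evaluations within an individual". That section describes no group-level term.

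The section on sample size and power rests the secondary hypotheses on the arm-by-time interaction for continuous outcomes. It claims 90% power at d = 0.23 with 114 participants, "assuming ICC of 0.20 for within-person (between-assessment) and ICC of 0.07 for within therapy group variation". Clustering by therapy group is therefore expected.

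On timing, the section on assessments defines the visits as "enrollment in the trial (T1), completion of treatment (T2), and three months post-treatment completion (T3"). The recruitment section places allocation after the eligibility interview: "If the young person meets the inclusion criteria, the intake worker will then allocate to treatment condition using the randomized allocation sequence".

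**The concern.** Families enrol, are assessed and are then allocated. Only afterwards do they sit in a therapy group with other families. Shared therapists and group dynamics can make outcomes alike within a group at T2 and T3, but not at T1.

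A random intercept for group, in its usual form, is one value per group added at every visit. In a comparison of change from T1 it is subtracted from itself. The model would contain a group term, yet the standard error of the test of interest would not reflect the group effect that arises during treatment. That effect would be left in the residual as if it were independent noise between families.

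At stake are the youth and parent mental health and relationship hypotheses measured on continuous scales. A few groups that did unusually well or badly could pass for a difference between BEST MOOD and PAST.

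**Working it through.** **Inputs from the protocol article (sample size and power):** therapy-group ICC 0.07 and within-person ICC 0.20 for continuous outcomes; 114 analysed, so 57 per arm; two-sided alpha 0.05.

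**Assumed:** 4 to 10 families per group (size not stated); all of the 0.07 arises at T2 and T3; variance 1 at each visit; complete data.

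**The plan's own figure.** The article gives no false-positive rate for the interaction. Its nearest figure is 90% power at d = 0.23. Without group clustering, a repeated-measures interaction test with 114 people, three visits and within-person correlation 0.20 has noncentrality 114 × f² × 3 / 0.80.
- With f = d/2 = 0.115 this is 5.65, and power is 55%.
- With f = d = 0.23 it is 22.6, and power is 99%.

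Neither gives 90%, so that figure was not reproduced. It is not used below.

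**Step 1: cancellation.** Let b be a group intercept common to all visits. For a member of that group, the change from T1 to T3 is (b + person + time effect + e3) − (b + person + e1). Both b and the person effect drop out. The modelled standard error then rests on residual variance alone, just as it would with no group term.

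**Step 2: variance of change.** With variance 1 at each visit and covariance 0.20, the variance of a family's change is 1 + 1 − 2 × 0.20 = 1.60. Of this, 0.07 is shared within the group, because it is present at T3 and absent at T1. The ICC of change is 0.07 / 1.60 = 0.044.

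**Step 3: design effect and error rate.** For m families per group, the design effect is DE = 1 + (m − 1) × 0.07 / 1.60. The true standard error is √DE times the modelled one. The false-positive rate is 2 × [1 − Φ(1.96 / √DE)].

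| m | DE | √DE | Modelled SE too small by | False-positive rate |
|---|---|---|---|---|
| 4 | 1.131 | 1.064 | 6.0% | 6.5% |
| 6 | 1.219 | 1.104 | 9.4% | 7.6% |
| 8 | 1.306 | 1.143 | 12.5% | 8.6% |
| 10 | 1.394 | 1.181 | 15.3% | 9.7% |

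**Step 4: simulation with no true effect.**
- *Change scores* (20,000 replicates; residual variance set so that the variance of change was 1.53): 6.3%, 7.8%, 8.7% and 9.9% for m = 4, 6, 8 and 10. A t test on group-mean changes gave about 5%.
- *REML mixed models over three visits* (400 replicates; joint test of arm by time):

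| Families per group | Groups per arm | Group intercept at all visits | Group effect at T2 and T3 only |
|---|---|---|---|
| 8 | 7 | 9.3% | 5.8% |
| 5 | 11 | 7.3% | 6.5% |

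- *A separate REML simulation* (500 replicates, 10 groups of 8 per arm) gave 7.8% with the all-visit intercept.

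The REML rates carry a Monte Carlo standard error of about 1.2 to 1.4 percentage points. They agree with Step 3 but do not fix its decimals.

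**Step 5: binary primary outcome.** Every participant has a depressive disorder at T1 by the inclusion criteria. With categorical time the T1 contrast is separated and cannot be estimated. A logistic mixed model with linear time, group ICC 0.17, 8 per group and an assumed person variance of 1.5 rejected in 0.8% of 132 replicates with the all-visit intercept. There was no inflation.

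**The case against.** The strongest reply is that the article never says the group effect is constant over visits. Random effects for group, in the plural, could include a group-by-time effect. The exact form of a cluster term is commonly left to an analysis plan, which is not shown here. The statement about covariance within an individual does not say that nothing else will be modelled. All of this stands, and it makes the point conditional. It does not remove it. The abstract's phrase in its ordinary sense means an intercept, the analysis section describes no group term, and neither structure protects the interaction test for which the article claims power.

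The size also depends on assumptions. The article reports difficulty in filling groups, so small groups are plausible, and they lie at the low end of the range. It does not say which visits the pilot ICC reflects. If half of the 0.07 were already shared at all visits, the rate would be about 6.5 to 7.5% with 8 per group and 5.3 to 7.2% with 4 to 5. That too is an assumption.

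Finally, groups fill from rolling recruitment in Melbourne and Geelong, so members may be somewhat alike at T1. A model that forces the baseline group effect to zero would be stricter than necessary.

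**Conclusion.** The point holds in conditional form for the continuous secondary outcomes. If the group term is a random intercept common to all visits, or is omitted, the arm-by-time test at nominal 5% rejects about 6 to 10% of the time under no effect. This rests on the article's ICCs of 0.07 and 0.20, on 4 to 10 families per group, and on the group effect arising after T1. Cancellation is exact only for a linear model with complete data and an unconstrained baseline. Carrying the last observation forward, as planned, moves the data towards completeness.

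A reader might infer three stronger things that the article does not support:
- That the planned tests certainly ignore clustering. No passage says that the group effect is constant over visits.
- That the primary remission test is inflated. It is binary, everyone is a case at T1, and the one scenario simulated showed no inflation.
- That the rates are well above 10%. Such figures come from a group ICC of 0.17, which the article gives for the primary calculation and not for the continuous outcomes.

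**What to change.** In the linear mixed models, state that the therapy-group random effect differs between baseline and post-treatment visits: a group-level random coefficient on a post-baseline indicator. Keep a baseline group intercept as well only if the data support it. Give each family that never joins a group its own singleton cluster, so that it stays in the intention-to-treat set. A t test on group-mean changes is a simple check on the result.

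The cost is one model term. Standard errors for arm by time grow by about 6% with 4 families per group and 18% with 10 (√DE of 1.064 and 1.181). That increase is uncertainty already present in the data, and power for these outcomes falls accordingly.

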**Trial registration:**

Australia and New Zealand Clinical Trials Registry Title: engaging youth with high prevalence mental health problems using family based interventions; number 12612000398808. Prospectively registered on 10 April 2012.

## Background

There is increasing community and government recognition of the magnitude and impact of adolescent depression in Australia and worldwide. The Australian National Survey of Mental Health and Wellbeing conducted in 2007 suggested that approximately one in four adolescents experienced a mental disorder in the 12 months prior to the survey [1]. However, less than one in four of those attended a professional service during the preceding six months [2]. The incidence of mental illness in young people is the highest of any age group. Seventy-five percent of adults suffering from disorders such as substance use, mood, and anxiety disorders had an onset age before 24 years [3]. During adolescence, it has been estimated that between four and eight percent of youth meet criteria for a major depressive disorder in American studies, with a 20% cumulative incidence rate for depression in community samples by the age of 18 [4,5]. One of the most significant concerns in adolescent mental health is the elevated risk for suicide in adolescents with depression. Suicide is the second leading cause of death of young Australians aged 15 to 24 years [6]. Adolescent suicide victims are approximately six and a half times more likely to have been struggling with alcohol or drug abuse, and 27 times more likely to have been suffering from a major depressive disorder at the time of their death; compared with demographically matched community control participants [7].

These multifaceted and complex mental health problems, occurring within a developmental context and interacting with family factors, means that the traditional mental health service delivery and intervention models have limited success. This is compounded by the findings that less than a quarter of youth who have diagnosable mental health issues actually receive services [1,2]. In families where conflict and detachment are prevalent, parents may have a limited capacity to engage youth in treatments [8], while young people themselves often have little motivation to attend services [2]. An increasing number of young people currently grow up experiencing alcohol or drug use and mental health problems, resulting in prolonged financial and material dependence on their parents [9].

### Treatments for adolescent depression

The evidence for treatments of adolescent depression is less well established than for adult populations [8]. A number of comprehensive reviews and meta-analyses show that there is limited evidence and the existing findings have not established the efficacy for either pharmacological or current psychological therapies for youth depression, anxiety and comorbid alcohol or drug abuse [10-12]. A number of psychological therapies have been supported for use with depression, anxiety and alcohol or drug abuse in adult studies, and have some limited support for use with adolescents. The most well researched individual therapy for depression and anxiety are cognitive behavioral therapies (CBT) which are well supported as a treatment for depression and anxiety in adults, but the evidence for the efficacy of these treatments with youth is much weaker [8,13-15]. The key point, however, is that individual treatment models presuppose the willingness of an adolescent to recognize problems, engage with services and complete treatments, which is very frequently not the case [16].

### Family as a target for intervention

Family-based interventions may prove to be effective for depressed adolescents, by: (i) enhancing youth engagement, (ii) targeting interactions between family members and resolving conflict, (iii) increasing support and family cohesion, (iv) reducing exposure to stressors within the family, and (v) maintaining adolescents within protective family environments for a longer period. There is evidence to suggest that depressed youth who are also in conflicted parent-child relationships are less responsive to individual treatments [17]. There is also substantive evidence from cohort studies that risk factors for depressive and anxiety symptoms are predicted by poor parent-child relationships, high family conflict, poor family attachments and detachment from family activities [18,19]. Given the evidence for family influences, researchers have repeatedly called for the development of prevention and early intervention programs that target family factors including assisting parents to create a warm and supportive family environment, appropriate parental monitoring and the use of authoritative parenting approaches across adolescence [20]. The other major advantage of family-based interventions is that they allow an avenue by which young people who are initially reluctant to acknowledge problems or attend services can be gradually engaged via other family members attending the service and showing a motivation for change.

Based on clinical experience and prior feedback from local services in an Australian context, if a concerned parent contacts a youth mental health service but the young person is unwilling to engage in treatment, the service is often unable to offer a program for the family. At most, a parent support session or support group may be offered to parents. In many cases, parents are informed that unless their adolescent is willing to attend, no service can be offered.

The current randomized controlled trial was designed to evaluate the capacity of family based interventions to: i) reduce the depressive symptoms of young people (12 to 18 years) and improve the mental health of their parents; ii) engage adolescents reluctant to use mental health services individually by working therapeutically with the whole family unit; and (iii) improve family functioning in the context of adolescent depression.

### The development of the BEST MOOD intervention

The intervention to be evaluated is known as the Behavior Exchange Systems Training (BEST MOOD) program and has been developed over three distinct stages. The original BEST intervention was initially developed as a multifamily group education program for parents, to be delivered by a mental health professional trained in the model [21,22]. The content of the initial BEST program focused on alcohol and drug use by adolescents. This version of the program was shown to reduce parental mental health symptoms and family stresses [23]. To increase efficacy for the youth themselves, the second stage of development (BEST Plus) included siblings who join their parents in the group for the final four weeks of the eight week program. Evaluations showed additional positive changes in the family system were produced in mental health and stress symptoms, family cohesion and increases in action by young people to address their substance use [9,24-26]. The third major development of the intervention model, the current BEST MOOD intervention, involved further developing the program as a broader intervention suitable for adolescents who present with depressive disorders [27]. The development of BEST MOOD was motivated by the predominance of adolescent depression in community referrals to previous evaluations and our discovery of an increased motivation of depressed adolescents to attend the final four sessions of BEST Plus. Accordingly, content was designed specifically to invite the adolescent to attend parallel sessions with their parents for the final four sessions and for depressed adolescents to benefit therapeutically from these sessions. The additional content in BEST MOOD was designed to complement the messages delivered to parents concerning improved family functioning, stress regulation, improved communication and resolution of major life events in the family’s history. This paper describes the design of an RCT to evaluate BEST MOOD.

